#### F0 declination in Estonian

This study investigates the impact of WM on conceptual processing and advance planning of sentence intonation based on Estonian. Estonian presents a good test bed for investigating declining intonation contours for three main reasons. First, many researchers have noted that Estonian sentence melody is mostly falling (overview in [73]). In the terminology of the autosegmental-metrical theory of intonation, a low edge tone occurs most frequently at the ends of intonation phrases [74]. Second, pitch accents occurring very regularly on most of the content words are F0 falls (F0 maxima followed by F0 minima; H*+L) [75]. Third, a recent corpus investigation has demonstrated length-dependent F0 raising at the beginnings of prosodic phrases randomly extracted from conversational speech [13]. The fact that the falling pitch accents are most frequent and that they mostly combine with low boundary tones indicates a rather small intonational inventory when compared to fully-fledged intonation languages like English or German. This tonal uniformity is well-suited for measuring F0 maxima in comparable tonal contexts, to replicate the effect of length on sentence-initial intonation peaks, and to examine the effect of cognitive load on the advance planning of sentence intonation.

### Hypotheses

In line with earlier studies, active sentences uttered in response to complex visual scenes are assumed to be produced less rather than more incrementally [15, 32, 35, 65, 76]. Oppermann et al. [76] show for German that sentences with a frequent subject-verb-object ordering (e.g., ‘Die Maus frisst den Käse’, ‘The mouse is eating the cheese’) can be successfully planned in full even at the phonological planning stage. For English, Ferreira and Swets [35] similarly demonstrate that speakers plan their active sentences non-incrementally when no time constraint is imposed. Therefore, this study of Estonian assumes that the conceptual planning under low cognitive load is only weakly incremental or even non-incremental, but it is expected to become more incremental when additional cognitive load is imposed, i.e., under high cognitive load. In other words, if conceptual planning processes share resources with WM, then the detrimental effect of high cognitive load should show increase in the incrementality of conceptual planning. The effect of cognitive load on the incrementality should be observable in the increased proportional duration of the naming gaze at the actor first mentioned before the onset of speech.

As argued in the previous paragraph, sentence planning is expected to proceed weakly incrementally or even non-incrementally under low cognitive load. Accordingly, tonal variation is expected to be determined by the number of concepts maintained in the WM or by sentence length such that sentence-initial intonation peaks are higher in longer than shorter sentences. The high cognitive load and the incrementality of planning are predicted to be tightly interrelated with the advance planning of sentence intonation. First, the incrementality is expected to relate to low pitch peaks because the highly incremental conceptualization processes only foresee mentioning the first concept in subsequent utterances. Second, the cognitive load is predicted to increase the sentence-initial pitch peaks given that the mental load arising from maintaining a complex conceptual network in WM (as it may occur whilst planning long but not short sentences) is comparable to the mental load that emerges from memorizing a word list. Consequently, two different outcomes of the load manipulation on sentence-initial intonation peaks are possible (see Fig 1).

**Fig 1 pone.0259343.g001:**
[figure not shown]
Illustration of hypotheses regarding sentence-initial intonation peaks based on the invented data. Error bars indicate the 95% confidence intervals.

First, regardless of sentence length, the pitch peaks could decrease to a level lower than the pitch peaks in short sentences under the low cognitive load. In this scenario, the high cognitive load affects short as well as long sentences, and the effect of high cognitive load is greater on long sentences than short sentences. Second, the effects of incrementality and the high cognitive load could accumulate such that, regardless of sentence length, the pitch peaks under the high cognitive load are about the same height as the pitch peaks in the short sentences under the low cognitive load. This scenario predicts the high cognitive load to affect the pitch peaks in long sentences but not short sentences.

## Materials and methods

A picture description experiment was designed to examine the effect of cognitive load on the incrementality of conceptual planning processes, and the effects of cognitive load and the resulting incremental planning processes on sentence-initial intonation peaks. The design and analysis methods are registered prior to collecting data and the Ethics Commission at the University of Tartu approved the experiment (3271T-27).

### Materials

The materials consist of pictures showing transitive events and lists of three unrelated nouns and verbs for the verb probe task. The pictures depict three actors, two of whom share a thematic role. The two core roles of transitive events typically include i) an initiator or agent, and ii) a undergoer of the action or patient. The two thematic roles are distributed amongst the three pictured actors such that either two agents act upon a single patient (Fig 2a and 2b) or a single agent acts upon two patients (Fig 2c and 2d). This constitutes a two-level factor called Double Actor with two levels: agent and patient. A further visual factor that the design manipulates is called Identity. The two actors in the same thematic role either do or do not share their identity (e.g., they are both donkeys or they are a donkey and goat). Thus, the factor Identity includes two levels: same and different. The two visual factors with two levels are fully crossed, resulting in four pictorially controlled conditions. In particular, the four conditions show (i) same multiple agents acting on a single patient (e.g., farmers pulling a donkey), (ii) different multiple agents acting on a single patient (e.g., a male and female farmer pulling a donkey), (iii) a single agent acting on similar multiple patients (e.g., a farmer pulling donkeys), or (iv) a single agent acting on different multiple patients (e.g., a farmer pulling a donkey and goat).

**Fig 2 pone.0259343.g002:**
[figure not shown]
An example picture in four experimental conditions eliciting short and long sentences.

The aim of this fully crossed two-factorial design is to elicit transitive sentences that differ in length, such that the similar double actor condition elicits short sentences and the different double actor condition triggers speakers to produce long sentences. The concrete task setting will ensure that the picture description will indeed be either short or long. In particular, participants are asked to describe the pictures by mentioning all three actors. Moreover, they are trained to use either plural NPs for the actors sharing the identity (e.g., ‘donkeys’) and coordinated NPs for the actors differing in the identity (e.g., ‘a donkey and a goat’).

The complex two-by-two design is necessary for the manipulation of the length effect at the two syntactic positions. This means that either the sentential subjects of prospective sentences are short or long (e.g., Mees sikutab eesleid, ‘The man is pulling the donkey’ vs Mees ja naine sikutavad eesleid, ‘The man and the woman are pulling the donkey’), or the sentential objects vary between short and long (e.g., Mees sikutab eesleid, ‘The man is pulling donkeys’ vs Mees sikutab eeslit ja kitse, ‘The man is pulling the donkey and the goat’). This design allows researchers to control for the possible interactions between the prosodic phrasing and F0 declination [4], and observe the effect of cognitive load in a worst-case scenario where the pitch peaks do not increase together with the length of object NPs.

Altogether, 64 different pictures of simple events (target items) are created for the study (4*64 = 256 pictures in total). Another set of 84 pictures will serve as distractor items. The distractor items will depict a variety of transitive and intransitive events comprising one to four identifiable actors. Half of the pictorial items are combined with a verb probe task separated into a second experimental block.

For the verb probe task, two sets of verbs are selected based on their collocation frequencies in the Estonian National Corpus [77]. The sets of transitive and intransitive verbs are restricted to participate in a moderate numbers of collocations with nouns referring either to animate (marked for subject function) or inanimate entities (morphologically marked for object function). The moderacy restriction (the co-occurrence frequency being between the Leipzig lexical frequency classes of 8 and 12 [78]) is applied for two reasons. First, when the verb participates in a small number of collocations that also occur frequently in the corpus, the verb might aid the recall of the memorized words. Second, and conversely, when the verb participates in a large number of collocations, it may be difficult to delimit the set of nouns that are conventional with these verbs. While the transitive verbs are selected such that they are free to occur with both animate and inanimate referents, the intransitive verbs are determined to encode actions typical for only animate referents.

The memory lists of three nouns are constructed such that they contain a noun that refers to an animate referent and two nouns that refer to inanimate referents. Notably, the variation of animacy in to-be-memorized word lists is regarded as the conceptual aspect of intended messages. The recall task builds on the semantics of verbs. In particular, the lists of nouns (e.g., traditsioon ‘tradition’, otsing ‘search’, investor ‘investor’) are selected such that all nouns are likely to occur with transitive verbs (e.g., jätkama ‘continue’) but only nouns referring to animate referents are conventional with intransitive verbs (e.g., muretsema ‘worry’). Half of the target trials in the second block will be prompted together with transitive verbs and the other half of the trials with intransitive verbs. The correct answers of the verb probe task (whether all of the nouns do conventionally/usually co-occur with the verb in the same sentences or not) have been confirmed in a pre-test with a different sample of native Estonian speakers. To balance the factor of verb type, 50% of distractor trials will be presented with nouns that are incompatible with the transitive verb prompt. Conversely, the other half of the distractor trials will be prompted together with intransitive verbs that are compatible with all of the nouns on a list. Due to the limitations of time and financial resources, the lists and prompts that are combined with distractor items are selected based on the corpus statistics and will not all be pre-tested.

Finally, another set of 12 pictures (practice trials) is comprised of 6 pictures similar to the pictures in target trials and of another 6 pictures similar to the pictures in distractor trials. Similarly, 12 additional pairs of nouns and a verb are constructed for the practice trials.

### Design

The two visual factors Double Actor and Identity, as well as the factor Cognitive Load, all comprising two levels, will be fully crossed, resulting in eight conditions in total. The two-level fixed effect Cognitive Load reflects whether the picture was described while maintaining a list of nouns in WM or not (levels low and high). The trials with no load constitute the first block of the experiment (32 target pictures) and the trials with the load (32 target pictures) constitute the second block.

Four lists of target trials are created by distributing the 256 target pictures between the four conditions (Double Actor crossed with Identity) using the Latin square approach. Target pictures in lists are distributed between the same set of 84 distractor pictures such that there are one or two distractor items for every target item, resulting in 148 experimental trials per list in total. Another set of four lists is created where the leftward placement of agents is reversed, resulting in eight lists. For the verb probe task, all eight lists are reversed for a further set of eight lists, amounting to 16 lists altogether. In all 16 lists, the second half of the trials include the verb probe task.

Participants are presented with all eight conditions across 64 target pictures (repeated measures, within-subject, between-item). The within-subject design is necessary because F0 tends to be highly variable and affected by many other, also non-linguistic, factors. The tonal differences between the conditions can most reliably occur within a speaker, ideally also within the items of the same speaker. Due to this practical limitation, most of the classical intonation research typically records all conditions for a speaker (see e.g., [4, 6–11, 46–49]). The within-item design is not optimal for the purposes of this study, as we aim to record genuine planning processes. Thus, the repeated measures design with within-subject and between-item factor represents the best fit between the purposes of the study and the limitations of the F0 measurements. In other words, the design resembles the ANOVA repeated measures design with a within-subject factor eliciting 64 measurements (8 images X 8 conditions) per participant.

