### Procedure

Subjects will be recruited through university mailing lists. The study call will include a registration form that requests subjects to share information about their age, linguistic background, vision and language impairments, if known. Invitations are sent to subjects who conform to the study criteria (see above). Otherwise, the subjects will be thanked for their interest. Together with an invitation letter, subjects will also receive a letter reminding them about their responsibility not to spread any infections, especially COVID-19, and to respect the hygiene rules in the testing rooms.

Upon arriving at the recording room at the University of Tartu, subjects are asked to fill out and sign a consent form informing them about the risks of the study and their right to stop participating in the experiment at any time without any consequences. They will be introduced to the eye tracking method that is carried out with synchronous speech recording.

After these introductory parts, the subjects are asked to seat themselves in front of the desktop-mounted EyeLink 1000 Plus eye tracker and lean their forehead on the head support. The chin is left unsupported because the study requires subjects to speak.

Subjects will be semi-randomly assigned to the 16 lists of experimental trials such that each list will be seen five or six times. The order of the items within a block (low vs high load) is randomized. The items are subdivided into the blocks such that there is the least possibility for semantic overlap between the target and distractor items.

Once the calibration procedures are completed successfully, subjects receive a thorough explanation of their task by seeing a sample of five pictures together with a possible written description in the bottom part of the screen. They will be given an opportunity to ask as many clarification questions as needed.

The subjects’ task is to describe simple actions by mentioning all three depicted actors using either plural or coordinated NPs. Every picture is presented for 6500 ms (Fig 3). The speech recording starts at the exact moment that the picture is shown. When the task is clear, subjects will have 6 practice trials to rehearse, after which they can again ask questions. If necessary, subjects are calibrated once more before proceeding to the experiment.

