**Fig 3 pone.0259343.g003:**
[figure not shown]
Presentation sequence of stimuli in trials without the concurrent memorization task.

Pictures are presented contingently to gaze. This means that a picture is only shown once the eyes move to the dot in the upper part of the screen. The gaze-contingent presentation ensures that subjects will always look at the dot in the upper part of the screen before seeing the picture. This procedure guarantees that all speakers begin processing of visual information at approximately the same time in all trials. Apart from the drift check, the experiment can proceed without any assistance or control from the experimenter and be interrupted at any point either for a break or quitting.

A break is enforced half-way through the trials to stimulate concentration on the task and to introduce the second block with the trials that are accompanied with the memorization task. First, subjects are presented with 6 practice trials with a task to memorize three words in their exact order and then after 2500 ms, to orally recall the memorized words and then indicate whether all of the memorized words are conventional with the verb on the screen or not. In particular, their task is to say if all of the words fit with the verb on the screen or not by either saying ‘Kõik sobivad’ (They all fit) or ‘Ei sobi’ (Not all words do fit). In the target trials, a correct response to a transitive verb prompt is that all words fit with the verb on the screen. For example, a ‘tradition’ or ‘search’ from the example in the Materials section (traditsioon, ‘tradition’, otsing, ‘search’, investor, ‘investor’) can be ‘continued’ and an ‘investor’ can ‘continue (with)’ something. The correct response to the intransitive verbs is that not all of the words fit. Consider the verb ‘worry’ paired with the nouns ‘tradition’, ‘search’ and ‘investor’ as an example. A ‘tradition’ or ‘search’ cannot ‘worry’ but an ‘investor’ can. Indeed, it is possible to worry about a tradition or search. However, within this particular task setting, this did not occur to our sample of the norming study because the accuracy scores for this word list was 1.0 when presented with the transitive verb ‘continue’ and 0.83 when presented with the intransitive verb ‘worry’. The target items are combined with pairs of nouns and a verb with the highest accuracy scores (see S1 Table).

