**Fig 5 pone.0259343.g005:**
[figure not shown]
Hypothetical onset latencies (left edge of bars) and duration (widths of bars) of gazes directed to a particular area of interest (e.g., blue refers to the agent initiating and orange to the patient undergoing the action of pulling) during the description of an item ‘man pulling a donkey’ in Estonian. The numbers on the squares count the gazes. The black vertical line indicates the speech onset latency. The red ellipse highlights the gaze that is called ‘naming gaze’ and defined as a gaze of longest duration prior to the start of an utterance. For assessing the degree of incrementality, the duration of the naming gaze is divided by the speech onset latency (for similar analysis procedures and data see, e.g., [19]).

Finally, F0 maxima and F0 minima are automatically extracted within the boundaries of agent and patient names and the boundaries of sentence-final words in cases where patient names do not occur at the end of a sentence (e.g., some sentence modifier (e.g., varsti, ‘soon’) follows the patient name). F0 maxima and minima measured in hertz (Hz) will be converted into semitones relative to speaker means based on Eq (1)
$$\begin{array}{c} F0_{st}=12*log_{2}\left(\frac{F0_{Hz}}{F0_{mean}}\right), \end{array}$$
(1)
where *F*0_*mean*_ is the subject’s mean F0 aggregated over all F0 contours extracted from all of the subject’s utterances. This method of converting F0 into semitones has the benefit of partly cancelling out the large-scale, gender-based differences in voice pitch (males typically have lower voice pitch than females). The effect of sentence length on sentence-initial pitch peaks is expected to be smaller than the gender effect. When gender variation in voice pitch is included in the data, the critical effects of sentence length and WM may remain unrevealed.

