#### Statistical analysis

The goal of the statistical analyses is to determine whether the scaling of sentence-initial pitch peaks in long sentences is affected by an independent effect of incrementality or by the simultaneous effects of incrementality and high mental load. As the manipulations of the factors Double Actor (agent vs patient) and Identity (same vs different) elicit short and long sentences (see in Materials), the combinations of these are reduced into a factor Sentence Length (short vs long) for the main analysis. Thus, the main analysis examines the effect of the interaction between Cognitive Load (low vs high) and Sentence Length (short vs long) on (i) the proportional duration of naming gazes at the first-mentioned actors, (ii) duration of naming gazes, (iii) the sentence-final pitch valleys, (iv) and the sentence-initial pitch peaks.

The four dependent variables (duration of naming gazes, proportional gaze durations, sentence-final F0 minima, sentence-initial F0 maxima) are modelled with separate linear mixed-effects regression analyses (LMER, as implemented in the *lme4* package in [82, 85]). All models include the interaction between Cognitive Load (low vs high) and Sentence Length (short vs long) as the fixed effect, the block and trial number as the covariate effects, and random intercepts and slopes for items and subjects. The analysis will be carried out using sum-to-zero coding of the fixed effects. To avoid the convergence issues, the models will be optimized following the procedures suggested in Bates et al. [82]. First, the continuous variables block and trial are centred and/or scaled for the statistical analyses. Second, the convergence tolerances are adjusted by applying an optimizing algorithm diverging from the standard test but which results in the converging model. Third, and only in case the previous measures do not yield the convergence of the model fit, the random effects structure will be simplified by removing the correlations term from the random effects structure. Finally, the significances of the model estimates are obtained with the help of the *lmerTest* package [86] in R [85]. The significances of the main effects and the interaction are determined at the threshold of p<0.05.

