The exploratory analyses inspect the three-way interaction between the factors Double Actor (agent vs patient), Identity (same vs different) and Load (low vs high) on (i) the proportional duration of naming gazes at the first-mentioned actors (ii) and the sentence-initial pitch peaks. The first exploratory analysis of naming gazes aims to determine whether the pictorial scenes combining the similar and differing event participants either in agent or patient role would induce planning increments differing and gradually increasing in size. Known from the studies relying on the grouping effect (though with moving displays), the chunk conceptualized and planned before the speech onset increases together with the more complex phrase structures [37, 38]. The second analysis will assess whether the length-dependent pitch raising depends on the syntactic position of the length variation (as in [4]). If a large number of sentences will be uttered with a break between the subject noun phrase and the verb phrase, the desired significant interaction with Identity (i.e., Sentence Length) and Cognitive Load might only occur when Double Actor corresponds to the agent. The models of the exploratory analyses and the significance testing will follow the same procedures as described for the main analyses.

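### Agent side is counterbalanced across lists but is not a term in the naming-gaze models; if side is mixed within lists, a little precision is lost

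*Protocol article*

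**What the plan says.** The Design section starts from four Latin-square lists and mirrors them: "Another set of four lists is created where the leftward placement of agents is reversed, resulting in eight lists". A further step doubles the set: "For the verb probe task, all eight lists are reversed for a further set of eight lists, amounting to 16 lists altogether". Under Procedure, subjects are "semi-randomly assigned to the 16 lists of experimental trials such that each list will be seen five or six times". Agent side is therefore a deliberate counterbalancing factor, known for every trial from the list assignment.

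The Statistical analysis section gives the model content: "All models include the interaction between Cognitive Load (low vs high) and Sentence Length (short vs long) as the fixed effect", together with "the block and trial number as the covariate effects, and random intercepts and slopes for items and subjects". On the exploratory analyses it adds: "The models of the exploratory analyses and the significance testing will follow the same procedures as described for the main analyses". Neither agent side nor list is named as a term.

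Two other statements matter. The incrementality outcome is spatial in origin, since it is built from gazes at agent and patient areas: "For assessing the degree of incrementality, the duration of the naming gaze is divided by the speech onset latency" (caption to Fig 5). The starting eye position is standardised: "a picture is only shown once the eyes move to the dot in the upper part of the screen" (Procedure). The article does not give that dot's horizontal position, does not say whether one list contains both placements, and does not give the size of any left-right effect on gaze.

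**The concern.** When a design balances a nuisance factor, the analysis normally carries that factor so that its variance leaves the error term. Here each picture is seen with the agent on one side by some subjects and on the other side by the rest. Side therefore varies within item, and the item intercept cannot absorb it. If side also varies within subject, the subject intercept cannot absorb it either, and the variance falls into the residual.

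The analyses affected are the two of naming gazes (proportional and absolute duration) and the first exploratory analysis. The first of these is the article's own check that the verb probe task reached conceptual retention, so its precision is worth protecting. The article also places 84 subjects at the limit of what is feasible, so precision gained from a model term is easier to obtain than precision from more subjects.

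**Working it through.** **Inputs from the article.** 84 subjects, 16 lists, 64 target trials per subject, threshold p<0.05 (taken as two-sided), nominal power 0.80. The 0.80 serves only as a reference point. It cannot be confirmed, because the variance defaults behind it are not printed.

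**Inputs assumed.** A left-right difference δ of 0.3, 0.5 or 0.8 residual SD.

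**List use.** 84/16 = 5.25, which agrees with five or six uses per list: 12 × 5 + 4 × 6 = 84. Eight lists carry each placement. If all four extra uses fall in one placement set, the split is 4 × 6 + 4 × 5 = 44 against 8 × 5 = 40. Taking that as the imbalance in a cell contrast with δ = 0.5 gives a rough shift of (44 − 40)/84 × 0.5 = 0.024 SD.

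**Reading A: both placements within a list.** A balanced two-level factor with difference δ adds δ²/4 to a residual variance of 1. If residual error made up the whole squared standard error, the SE ratio (term omitted over term included) would be √(1 + δ²/4). Power becomes Φ((1.960 + 0.842)/ratio − 1.960). If residual error is only half of the squared SE, the ratio is √(1 + 0.5 × δ²/4).

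| δ | 1 + δ²/4 | SE ratio, upper bound | Power, lower bound | Power, residual half of SE² |
|---|---|---|---|---|
| 0.3 | 1.0225 | 1.011 | 0.791 | 0.796 |
| 0.5 | 1.0625 | 1.031 | 0.776 | 0.788 |
| 0.8 | 1.1600 | 1.077 | 0.739 | 0.769 |

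A small simulation agrees. It used 84 subjects, 64 items, 16 lists, 67% of trials kept at random, subject and item effects fitted, and 25 repeats per setting. The SE ratios were 1.012, 1.031 and 1.079. With a true Load effect of zero, the mean Load estimate without the side term was 0.0019, −0.0002 and −0.0047. The Monte Carlo error is about 0.017/√25 = 0.0034, so no bias is visible.

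**Reading B: one placement throughout a list.** Side is then constant for each subject and is a linear combination of the subject indicators. A uniform side shift moves only the subject intercepts and leaves the Load and Load by Length contrasts untouched. In the simulation the SE for Load stayed between 0.0167 and 0.0169 as δ went from 0 to 0.8. Only a side-by-Load or side-by-Length interaction would remain, and it would sit in the subject slopes.

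**The case against.** The strongest objection is that no loss need arise at all. The sentence on reversing agent placement fits one side per list at least as well as mixed sides, and under one side per list nothing is lost. This stands, and it is why the point is conditional. A reader might infer from the missing term that a side effect is bound to inflate the error of the incrementality tests. The article does not support that.

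A reader might also infer bias from unequal list use and trial exclusions. The support is weak. The worst split is 44 against 40 subjects, and under one side per list every subject contributes all cells at the same side. The simulation dropped trials at random, so it does not test exclusions that depend on side. The rule on first fixations later than 400 ms could in principle depend on side. However, bias in the Load effect would need that dependence to differ between cells, and the article gives no reason to expect it.

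A third tempting reading converts the extra variance into lost trials: 0.0625/1.0625 = 5.9% at δ = 0.5 and 0.16/1.16 = 13.8% at δ = 0.8. These are upper bounds, because the models also carry subject and item variance and residual error is only part of the SE.

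It is also fair to say that counterbalancing already protects the estimates, that the starting gaze position is standardised, and that the outcome is the longest gaze and not the first. Leaving out a balanced nuisance factor is a legitimate choice. Finally, the article condenses a longer plan that may carry the term. Against that, the article does list the terms of its models, and it says that design and analysis methods are registered before data collection. Naming one more term there is reasonable.

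**Conclusion.** The point holds as a minor, conditional matter of precision. Agent side is balanced by design and absent from the stated model terms. If side is mixed within lists, the SE for Load and Load by Length in the gaze models is larger by up to about 1%, 3% or 8% for δ of 0.3, 0.5 or 0.8. At δ = 0.5 the cost is roughly one to two power points. If side is constant within lists, the cost is nil.

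The sizes rest on assumed values of δ, since the article gives none, and on 0.80 as the starting power. There is no sign of material bias under either reading. The analyses of sentence-initial peaks and sentence-final valleys are outside this point.

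**What to change.** State in the Design section whether a list mixes left and right agent placement or keeps one side throughout. Add agent side (left/right, sum-coded) as a fixed covariate in the models for proportional naming-gaze duration and absolute naming-gaze duration, and in the first exploratory gaze model.

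The variable is already known from the list assignment. The cost is one parameter per model, with no new data and no change to the hypotheses tested. If side turns out to be constant within lists, the term is a harmless between-subject covariate. Naming it before data collection also avoids a later post hoc decision to include it.
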